**Entomological evaluations**

Deltamethrin will be the AI deployed in ET. In addition, the standard pyrethroid-only net distributed in the study area is PermaNet 2.0, which contains deltamethrin. Long-term efficacy of the insecticide-treated ETs will be evaluated using periodic WHO cone bioassays to validate continued impact against resistant wild-type mosquitoes.

We will assess the impact of ETs on entomological measures of malaria transmission by measuring the density of *Anopheles* mosquitoes indoors on a monthly basis: in 20 clusters (10 ET, 10 control) in 10 randomly selected households per cluster. Per trial arm, 10 new clusters will be selected each month so that all study villages will be sampled bimonthly, as recommended by the WHO VCAG. In the 10 selected treatment clusters, we will select only ET-treated households. Mosquitoes will be captured indoors overnight using miniature CDC light traps placed next to a sleeper under an LLIN for 3 consecutive nights. These traps will be placed inside the house by Vector Control Product Evaluation Centre/Institut Pierre Richet (VCPEC-IPR) entomology technicians at 6 pm in the evening and collected by the technicians at 8 am the following morning. Mosquitoes will be sorted by Household ID and date of collection. Indoor temperature and relative humidity will be recorded in enrolled HHs during entomological sampling using data logging devices.

A subset of 10% of all caught mosquitoes will be identified by microscopy and the numbers of *An. gambiae* s.l. and other species recorded. In subsets of 10% of all caught anophelines, we will type to species level using PCR. Results will be used to estimate mean vector density and species composition per trial arm. For the *An. gambiae* and *An. funestus* samples in these subsets, we will assess the presence of sporozoites using CSP-ELISA. Sporozoite prevalence will be measured from a random sample of up to 60 anopheline females per cluster per sampling night.

We will estimate the EIR in each study arm (i*.*e.*,* mean number of sporozoite infective per bites per cluster per month) where we assume that a mosquito caught indoors and actively searching is able to bite the host.$$\mathrm{EIR}=\mathrm{Human}\;\mathrm{biting}\;\mathrm{rate}\;\times\;\mathrm{Sporozoite}\;\mathrm{rate}\;\times\;365=\frac{\mathrm{Number}\;\mathrm{of}\;\mathrm{mosquitoes}\;\mathrm{collected}}{\begin{array}{c}\mathrm{Number}\;\mathrm{of}\;\mathrm{capture}\;\mathrm{nights}\\\end{array}}\times\frac{\mathrm{Number}\;\mathrm{sporozoite}\;\mathrm{positive}\;\mathrm{mosquitoes}}{\begin{array}{c}\mathrm{Number}\;\mathrm{of}\;\mathrm{mosquitoes}\;\mathrm{tested}\\\end{array}}\times365$$

**Intervention quality monitoring**

Integrity of the intervention (e.g., damage to the ET inserts) in the treatment villages and general house condition in all villages will be monitored by quarterly village walk-throughs every 4 months by project staff in both study arms. In addition, a designated member of the study team will be available for householders to report ET-related construction problems and get them fixed during the trial.

The persistence of the chemical insecticide used on the inserts will be monitored bimonthly by taking a sample of inserts from the treated villages to the lab (these will be replaced with fresh inserts) and exposing mosquitoes to them in a controlled bioassay. We will use F1 adult female anopheline mosquitoes reared from field-collected eggs in WHO cone tests with a 3-min exposure and mortality monitored 1 day post-exposure. Mortality will be compared against equivalent mosquitoes (wild-type resistant) exposed to untreated “control” inserts. Inserts will be replaced once the mortality post-exposure falls below 70% (from previous results, we expect this to be every 10–12 months).

**Data forms**

A combination of standardized paper-based or digital forms (under Android tablets) will be used. VCPEC-IPR and University of Notre Dame (UND)/Center for Research Computing (CRC) will work together to develop the quantitative forms to be uploaded on Android tablets. Entered data (entomological and epidemiological) will be automatically assessed for quality using established quality control rules, then reviewed, and appended to the data already present. Data forms can be made available upon request submitted to UND.

##### End of trial

The final clinical survey of the child cohort will take place at the end of the 24-month follow-up. The final light trap collection will take place at about the same time.

At the end of the trial, HH owners will be offered to have the ETs blocked with a closed insert or plastic cap to block the tubes. However, we intend to liaise with stakeholders throughout the trial to gage interest in providing continued retreatment for ET inserts after the trial, as is now taking place in Côte d’Ivoire.

##### Sub-studies

The sub-studies described in this section are not part of the WHO-approved clinical study design as they are secondary endpoints and not part of the primary evaluation of public health impact of the intervention.

We will conduct an assessment of key user acceptance indicators and cost-effectiveness of the ETs intervention vis-a-vis other alternative technologies or practices available. These sub-studies will be critical for successful scaling of the product, as they will help identify the most socially acceptable and sustainable way of achieving and maintaining high coverage of ETs. User acceptance does not always translate into adoption unless the intervention is found to be affordable and more cost-effective compared to other available options for malaria protection. In this regard, cost-effectiveness analyses are planned in this study.

**Cost-effectiveness studies**

A Global Health Economist within UND’s Keough School of Global Affairs will conduct an economic evaluation to estimate the costs and cost-effectiveness of the ETs intervention. The cost analysis will take the gold-standard, societal perspective which includes both provider and community costs. Implementation costs will be carefully monitored during ETs installation and maintenance activities. Data on incremental costs of the ETs product, house modifications during install, and their sources will be collected from project expenditure records. Household costs will be collected at cohort enrolment shortly after intervention installation, and the unit costs (cost per house and person) will be calculated. This cost study will demonstrate the costs of using ETs as a stand-alone tool compared to the previously combined intervention of SET.

The cost-effectiveness analysis will have the primary endpoint of cost per disability-adjusted life years (DALYs) averted by ETs. Incremental cost per DALY averted for ETs (Intervention arm) relative to LLINs alone (control arm) will be calculated using the epidemiological data collected during the trial. Cost-effectiveness ratios will be presented as point estimates and ranges (using the confidence intervals (CIs) on the epidemiological data and reflecting any uncertainty in costs) and interpreted against a range of willingness to pay thresholds and in relation to the cost-effectiveness of other malaria control interventions.

Cost modeling will assess the cost-effectiveness of ETs compared to the previously applied SET intervention, and compared to standard vector control interventions such as LLINs and IRS. The potential cost-effectiveness of ETs at scale over time will be simulated to facilitate comparison with other malaria control interventions and cost-effectiveness benchmarks. We will measure the cost of ETs’ implementation in relation to manufacturing, efficacy, and coverage to model projections of cost-effectiveness to incentivize potential procurers.

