## Objectives {7}

### Main research question

This study intends to test whether ETs protect people against mosquitoes (entomological endpoints) and malaria (epidemiological endpoints) in an area where malaria transmission is driven by insecticide-resistant *Anopheles gambiae* mosquitoes.

The primary study objective is to assess whether ETs reduce the number of malaria infections and clinical malaria, defined by active case detection, in children between 6 months and 10 years of age, compared to children living in communities without ETs, in an area where there is universal coverage of LLINs (1 LLIN for every 2 people) and pyrethroid resistance is high.

Secondary objectives include:(i)To determine how ETs impact the rate of anemia (moderate anemia defined as 7–9.9 g/dL hemoglobin; severe anemia as < 7 g/dL hemoglobin)(ii)To assess how ETs impact Entomological Inoculation Rates (EIR) computed as the product of the anopheline vector density and the sporozoite rate, compared with LLINs alone(iii)To assess the cost-effectiveness of the ETs intervention(iv)To assess the user acceptance of the ETs intervention

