### Sample size {14}

The number of villages for the cRCT is estimated at 17 per treatment arm based on the power analysis which is detailed in the Statistical Analysis Plan.

The sample size determination on the required number of households per cluster for testing the primary hypothesis on PE is based on the hazard rate comparison in the proportional hazards regression model. With the following specifications: power = 80%, 2-sided type-I error rate = 5%.True PE/Minimum effect size = 35%Baseline first-time malaria infection hazard rate = 1.5 cases of falciparum malaria per person-year (conservative estimate based on control arm data from first SET cRCT)Coefficient of variation (k) = 40% (based on first SET cRCT)Loss to follow-up (LTFU) rate = 20%Monitoring = 2 years to capture 2 peak transmission seasonsOne interim analysis for efficacy and non-binding futility with the O’Brien-Fleming error spending function when 50% information is collected

With 17 clusters per treatment, 55 children (aged 0.5 to 10 years old) from 55 different households per cluster are expected to yield 1315 independent first-time malaria events with a 24-month follow-up period to yield 80% power in testing the primary hypothesis on PE. Since the sample size already factors in a 20% LTFU rate, there is no need for replacement subjects.

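### The planned range for cost per DALY averted becomes infinite or negative at its unfavourable end whenever the 95% CI for the malaria effect includes zero (about 17–20% of trials at the design effect); net monetary benefit would stay defined.

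*Protocol article*

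**What the plan says.** Secondary objective (iii) (Protocol article, Main research question) is "To assess the cost-effectiveness of the ETs intervention". The section Cost-effectiveness studies sets the endpoint: "Incremental cost per DALY averted for ETs (Intervention arm) relative to LLINs alone (control arm) will be calculated using the epidemiological data" of the trial. It then sets the reporting format: "Cost-effectiveness ratios will be presented as point estimates and ranges (using the confidence intervals (CIs) on the epidemiological data", also reflecting cost uncertainty, and "interpreted against a range of willingness to pay thresholds".

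The section names no net-benefit measure and no acceptability curve, and has no rule for an effect interval that includes zero. Outcomes {12} lists cost-effectiveness among the other pre-specified outcomes, and Sub-studies places it outside the WHO-approved design.

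**The concern.** A ratio is well behaved only while its denominator stays clear of zero. Here the denominator is DALYs averted, which depends on the malaria effect. As the lower limit of PE falls towards zero, cost per DALY averted grows without bound; below zero the ratio changes sign. A negative ratio caused by harm looks the same as one caused by savings, so it cannot be compared with a threshold, and that comparison is the use the section intends.

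The format therefore fails at one end when the effect is moderate or imprecise, which is also when the economic answer is least obvious.

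**Working it through.** **Inputs** (Sample size {14}): "power = 80%, 2-sided type-I error rate = 5" per cent; "True PE/Minimum effect size = 35" per cent, so HR 0.65 and ln HR = −0.4308; control rate "1.5 cases of falciparum malaria per person-year"; between-cluster CV 0.40; 17 clusters per arm; 55 children per cluster; 24 months; 20% loss to follow-up; 1315 expected first events. The final critical value of 1.9744 and interim boundary of 2.7965 come from the primary-analysis text.

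**1. Reproduce the plan's figures.**
- Person-years per cluster: 55 × 2 × 0.8 = 88. Rates: 1.5 and 1.5 × 0.65 = 0.975.
- Hayes–Bennett: z = √{16 × 0.525² / [2.475/88 + 0.16 × (1.5² + 0.975²)]} = √(4.41/0.5402) = 2.857. Power is Φ(2.857 − 1.96) = 81.5%, against 80% stated.
- First events: 935 × 0.8 × (1 − e^(−3)) = 711 and 935 × 0.8 × (1 − e^(−1.95)) = 642. The total is about 1352, against 1315 stated (2.8% higher).

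The design is reproduced closely enough to use its precision.

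**2. Standard error of ln HR.**
- From events and CV: √(2 × 0.16/17 + 1/711 + 1/642) = 0.148.
- Back-calculated from exactly 80% power under the stated interim and final boundaries: required drift 2.81, so 0.4308/2.81 = 0.153.

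**3. Chance that the 95% CI for PE reaches zero.** P = Φ(1.96 − |ln(1 − PE)|/SE), for the full-follow-up estimate; early stopping is not modelled.

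| True PE | SE 0.148 | SE 0.153 |
|---|---|---|
| 35% | 17% | 20% |
| 30% | 32% | 36% |
| 25% | 50% | 53% |

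The Hayes–Bennett z gives Φ(1.96 − 2.857) = 18.5% at PE 35%. At a true PE of 38% with SE 0.153 the figure is 12%.

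**4. What the range looks like.** Assume that DALYs averted are proportional to PE. Let C be the incremental cost divided by the control-arm DALY burden, taken as fixed and positive. The ratio is then C/PE. With SE 0.153:

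| Observed PE | 95% CI for PE | Point ratio | Ratios at the CI limits |
|---|---|---|---|
| 35% | 12.2% to 51.9% | 2.9C | 1.9C and 8.2C |
| 25% | −1.3% to 44.5% | 4.0C | 2.2C and −77C |
| 20% | −8.0% to 40.8% | 5.0C | 2.5C and −12.4C |

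The first row is usable. In the other two, the limits do not bracket the point estimate. The set they stand for runs from 2.2C (or 2.5C) upwards through infinity to the intervention being dominated.

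**5. The same data as net benefit.** Per unit of control-arm burden, net benefit is λ × PE − C at threshold λ. For an observed PE of 25% and, purely as an illustration, λ = 5C, the point value is 5 × 0.25C − C = 0.25C. The limits are 5 × (−0.013)C − C ≈ −1.1C and 5 × 0.445C − C ≈ 1.2C. They are finite, correctly ordered and on either side of the point estimate.

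**The case against.** - **The computation is not spelled out.** This is one sentence in a condensed article, and it could describe joint simulation of effect and cost; a range of thresholds does not rule out an acceptability curve. That stands as to the mechanics. The reported object is nevertheless fixed as a ratio with a range drawn from the epidemiological CIs. Percentiles of simulated ratios would meet the same difficulty, because draws with harm give negative values that sort below the favourable ones.
- **One in five is roughly the complement of 80% power.** When the effect interval includes no benefit, an upper end that runs to dominated correctly says that cost-effectiveness is not established. This also stands. A reader might infer that the objective would be left with no usable statement of uncertainty; the documents do not support that, since the favourable limit stays interpretable and most trials at the design effect give a finite range.
- **The figures at 30% and 25% assume effects below the design value.** True; they are conditional. The 38% reduction in the earlier trial came from tubes plus window screening. The Introduction cites semi-field work suggesting that the tubes supplied most of it, but the tubes alone are what this trial tests.
- **Cost data by village may not exist.** The section lists project expenditure records and household costs taken at cohort enrolment, not treatment costs by village during follow-up. This stands, and limits the remedy.
- **The stakes are low.** Agreed: no primary or safety conclusion changes.

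**Conclusion.** The point holds as a modest improvement to a secondary sub-study. Whenever the 95% CI for the malaria effect includes zero, the unfavourable end of the planned range is infinite or negative and cannot be compared with a threshold. The expected frequency is about 17–20% at the design PE of 35% and about 32–36% at a true PE of 30%. This rests on three assumptions: the CIs referred to are those of the between-arm malaria effect, DALYs averted are proportional to that effect, and the incremental cost is positive.

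Two further readings are tempting but unsupported. A reader might infer that combining effect limits with cost limits gives the wrong coverage; the section neither says how they are combined nor claims a 95% level for the range. A reader might also infer that the plan ignores costs and effects moving together; the section does not say so, and does not list the treatment-cost data on which that link would depend.

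**What to change.** Keep the point estimate of incremental cost per DALY averted. Replace the range by incremental net monetary benefit (threshold × DALYs averted − incremental cost) with a 95% CI at each planned threshold, and add a cost-effectiveness acceptability curve.

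Obtain both from one loop: resample whole villages within arm, re-estimate the malaria effect, draw unit costs from their uncertainty, and apply the planned unit costs to each village's treated houses. This assumes no village-level treatment-cost data.

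The change is a few sentences in the economic analysis text and some extra analysis time. The downside is that net benefit is less familiar to some readers than a single cost-per-DALY range; keeping the point ratio beside it meets most of that.

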**User acceptance studies**

Social scientists from the Institut Pierre Richet will use quantitative methods to assess ETs’ adoption, adherence, and acceptability among study participants. Combined, endpoints from these assessments will inform potential bottlenecks to product access, uptake, and implementation post-trial.

Ethnographic data will be collected during the baseline population census to inform socio-economic status of households and participants. Adoption will be assessed using indicators of informed consent rates and ETs coverage rates in the trial. Adherence will be assessed via quality control monitoring of ETs’ integrity during the trial. User acceptance will be measured based on inhabitants’ willingness to pay and continue using ETs after the trial through an endline survey.

To design potential strategies for scale-up, we will identify and engage with key local, national, and international level stakeholders, involving them in discussions and creating a driving team to identify mechanisms for expansion and institutionalization while acting as advocates for the innovation.

#### Plans to promote participant retention and complete follow-up {18b}

Participant retention strategies include fostering relationships with participants, provision of community health worker and nurse contact information for easy communication to alleviate concerns, and periodic generation of retention rates to evaluate strategies.

#### Data management {19}

UND will achieve a systems approach to protocol adherence, implementation, data gathering, and sharing by installing a program monitoring plan (i.e., data gathering, training oversight, overall program progress) that will support rigorous data collection for policy recommendation. The UND CCRC will host the data server and will be responsible for data management, data form processing, and provision of support for training in-country collaborators’ data entry personnel.

Hardcopies of study and study-related documents (e.g., protocols, raw data, documentation, and final reports generated during a study, as well as chemical usage sheets) will be stored at VCPEC-IPR in a locked filing cabinet under the supervision of a designated archivist. Electronic data will be stored on UND servers with restricted access.

After study files have been held in the VCPEC-IPR for 5 years, the archivist will contact the sponsor to determine their future storage requirements. At the request of the Sponsor, it will either continue to be kept at VCPEC-IPR, sent to the Sponsor for storage, or destroyed. All hardcopies of documents will be destroyed by shredding and data on disks will be wiped, and the disks broken prior to disposal in the VCPEC-IPR waste.

#### Confidentiality {27}

Study subjects will be identified only by their study identification number and any electronic database will only contain their study identification number. Personal identifiers will be removed from the transcripts of interviews and discussions with participants being identified only through a study identification number. Thus, all data will be anonymized on data entry. The UND CRC databases will be password-protected and accessible only to authorized personnel. All hardcopy documents will be securely stored in locked filing cabinets and accessible only to authorized personnel.

The PI will maintain appropriate medical and research records for this study in compliance with the principles of good clinical practice and regulatory and institutional requirements for the protection of confidentiality of participants.

The authorized representatives of the sponsor, the ethics committee(s), or regulatory bodies may inspect all documents and records required to be maintained by the investigator, including but not limited to, medical records (office, clinic, or hospital) for the participants in this study. The clinical study site will permit access to such records.

#### Plans for collection, laboratory evaluation, and storage of biological specimens for genetic or molecular analysis in this trial/future use {33}

Not applicable. Study has no planned future uses for the biological specimens.

### Statistical methods

#### Statistical methods for primary and secondary outcomes {20a}

The baseline characteristics of the enrolled subjects, households, and clusters will be summarized by treatment arm (control arm, LLIN and intervention arm, ET + LLIN). Specifically, we will examine subject age and gender at the individual level, wall type and roof type, house open eaves, number of windows, number of doors at the household levels, and cluster population and baseline prevalence rate at the cluster level.

In the following analysis that involves malaria incidence, a child will not be considered at risk for malaria for 2 weeks after any treatment for malaria.

##### Primary

Protective efficacy (PE) against clinical malaria infection will be determined by comparing hazard rates of malaria clinical cases between the two treatment arms based on an intention to treat (ITT) analysis. The primary hypothesis on PE against overall malaria case incidence will be tested by comparing the hazard rates of the overall malaria case incidence between the control and ET in the ITT population using a proportional hazards model. The model will include relevant individual-level, household-level, and cluster-level baseline covariates, treatment assignment, and follow-up visits and random effects to account for correlations among the subjects within the same cluster and among multiple infections within the same individual. The hazard ratio $$\beta$$ between ET and control will be estimated, along with a 95% confidence interval. The null hypothesis of PE = 0% is equivalent to $$\beta =0$$, which will be tested by the Wald’s test $$z=\widehat{\beta }/s$$, where $$s$$ is the estimated standard error of $$\widehat{\beta }$$. There will be one formal interim analysis to test the primary hypothesis. The decision boundaries are calculated for either stopping for futility or stop for efficacy using the O’Brien-Fleming error spending function [8–10], with a 2-sided Type I error rate of 0.05, Type-II error rate of 0.2; baseline incidence rate of 1.5 per person-year, and between-cluster CV of 40%. The interim analysis will occur when 658 events (50% information) are collected. Assuming a baseline incidence rate of 1.5 per person-year, the interim analysis is estimated to occur around the end of Year 1 of the intervention follow-up. Due to the formal interim look at the data which costs a certain amount of type-I error rate and type-II error rates, the final critical value is different from what would be for a study without the interim look.

If the z-score of the log(hazard ratio) from the comparison between ETs and control at the interim look is >  − 0.7288 then the study can stop for futility (if *z*-score > 2.7965, the trial would stop for definitive harmful effects of ETs though the chance this would occur is close to 0 if not 0), the study can stop for futility. Since we adopt the non-binding futility boundary the study can continue to collect more data even if we cross the futility boundary at the interim look, there will be no inflation of type I error. In other words, the trial does not need to stop to accept the null hypothesis when the test statistic falls in the futility region at the interim stage. If the interim z-score <  − 2.7965 then the study can stop for efficacy. The study may also continue even if the efficacy boundary is crossed at the interim look, and there will be no inflation of type I error as efficacy is already established at the interim. If the interim z-score falls within (− 2.7965, − 0.7288), the study continues.

If the interim results do not cross either the futility or efficacy boundaries, the *z*-score from the final analysis upon the completion of the study will be compared with − 1.9744. If the *z*-score <  − 1.9744, we reject the null hypothesis, claiming ETs reduce the malaria hazard rate compared to control at the significance level of 5%; if the *z*-score > 1.9744, we fail to reject the null hypothesis, claiming ETs do not reduce the malaria hazard rate compared to control in Cote d’Ivoire. If the interim results cross either the futility or efficacy boundaries, the final analysis is only conducted for estimation purposes, as the futility or efficacy of ETs is already established at the interim.

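### The interim trigger of 658 events matches neither its 50% information label nor its end-of-Year-1 date: on the plan's inputs it falls at about 6 months

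*Protocol article*

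**What the plan says.** The Primary subsection of the statistical methods sets the trigger: "The interim analysis will occur when 658 events (50% information) are collected". It then says that, at a baseline incidence of 1.5 per person-year, "the interim analysis is estimated to occur around the end of Year 1 of the intervention follow-up". The test is a Wald z from a proportional hazards model with random effects for cluster and for correlation "among multiple infections within the same individual". The interim boundaries are −2.7965 for efficacy and −0.7288 for futility, and the final critical value is −1.9744. The text says they were derived from O'Brien-Fleming error spending with a between-cluster CV of 40%.

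The Sample size section gives the inputs: "Baseline first-time malaria infection hazard rate = 1.5 cases of falciparum malaria per person-year", PE of 35%, k of 40%, 20% loss, and 17 clusters of 55 children per arm. These "are expected to yield 1315 independent first-time malaria events with a 24-month follow-up period". The number 658 is half of 1315.

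**The concern.** Four statements have to agree: the event count, the information label, the calendar estimate and the boundaries. Two things suggest that they do not.

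- First events come early. At 1.5 per person-year most children have had theirs well before month 24, so half the total cannot take half the time.
- With villages randomised and k at 40%, much of the variance of the log hazard ratio is between villages, and more events per village do not reduce it.

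The interim decision is at stake. If a boundary is crossed, the protocol keeps the final analysis for estimation only. An efficacy claim could then come before the second peak season and before the 10 to 12 months at which insert replacement is expected. The stated boundaries would also not be those that the declared spending function gives at the actual look.

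**Working it through.** **1. Reproduce the plan's total.** Children per arm after loss: 0.8 × 17 × 55 = 748. Hazards: 1.5 (control) and 1.5 × 0.65 = 0.975 (ET). Expected first events by year t:

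E(t) = 748 × [(1 − e^(−1.5t)) + (1 − e^(−0.975t))]

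E(2) = 748 × (0.950 + 0.858) = 1352, which is 2.8% above 1315. With gamma-distributed cluster hazards (CV 0.4), each term becomes 1 − (1 + 0.16λt)^(−1/0.16) and the total is 1294, 1.6% below. The planned 1315 lies between the two, and 1315/2 = 657.5.

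**2. Date of event 658.** E(0.5) = 748 × (0.528 + 0.386) = 683, so event 658 falls at 5.7 months, or 6.0 with the gamma variation. E(1) = 748 × (0.777 + 0.623) = 1047, or 999 with gamma, which is 76 to 80% of 1315. If losses accrue over time or are ignored, event 658 comes at 4.2 to 4.7 months, but those versions give about 1415 to 1690 events at 24 months and so reproduce 1315 less well.

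Conversely, reaching 658 at month 12 needs a control hazard of about 0.71, and then only about 1020 first events accrue by month 24.

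**3. Information.** With two arms of 17 villages, Var(log HR) ≈ 2k²/17 + 4/E. At k = 0.40 the cluster term is 2 × 0.16/17 = 0.0188. The event term is 4/658 = 0.0061 at the look and 4/1315 = 0.0030 at the end. Information fraction: (0.0188 + 0.0030)/(0.0188 + 0.0061) = 0.0219/0.0249 = 0.88.

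| Residual k | Fraction at 658 of 1315 | Fraction at 1000–1047 of 1315 (month 12) |
|---|---|---|
| 0.4 | 0.88 | 0.96–0.97 |
| 0.3 | 0.82 | 0.93–0.95 |
| 0.2 | 0.72 | 0.89–0.91 |
| 0.1 | 0.58 | 0.81–0.84 |
| 0 | 0.50 | 0.76–0.80 |

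The label is right only without clustering. In that case the Schoenfeld formula needs 4 × (1.96 + 0.84)²/(ln 0.65)² ≈ 170 events for 80% power, so 1315 is itself a consequence of clustering.

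**4. Event type.** If all episodes count, 748 × (1.5 + 0.975) × 2 ≈ 3703 are expected. Then 658 arrives at 12 × 658/(2.475 × 748) = 4.3 months, or 3.4 months with 935 per arm and no loss. At k = 0.40 the fraction is (0.0188 + 0.0011)/(0.0188 + 0.0061) = 0.80, ignoring within-child correlation. At residual k = 0.2 it is (0.0047 + 0.0011)/(0.0047 + 0.0061) = 0.54.

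**5. Boundaries.** 2.7965 is the classical two-look O'Brien-Fleming value at t = 0.5. At t = 0.88 the pair would be about 2.13 and 2.05 (Lan-DeMets spending) or 2.16 and 2.03 (classical shape).

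At PE 35% and k = 0.40 the final drift is ln(0.65)/√0.0219 = −2.91, and the mean interim z is −2.91√t:

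| Information at look | Mean z | P(efficacy crossed) | P(futility crossed) |
|---|---|---|---|
| 0.50 | −2.06 | 23% | 9% |
| 0.88 | −2.73 | 47% | 2% |

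The two-sided type I error with the stated values at t = 0.88 is 0.048.

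**The case against.** The strongest reply is that nothing here makes a rejection invalid. That stands. A reader might infer that unsuitable boundaries inflate type I error, but it stays at about 0.048 because the efficacy value is stricter than the spending function requires.

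A reader might also infer that crossing a boundary ends the trial and loses the second peak season. The protocol lets the study continue after either crossing, calls futility non-binding and leaves the decision to the monitoring committee.

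The 0.88 is not a fixed fact. The model adjusts for baseline covariates, including cluster prevalence, and allocation may be stratified, so residual k may be below 0.40. With all episodes and residual k near 0.2, the fraction would be close to one half. But the look would then come at about 3.4 to 4.3 months, further from the stated date.

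It is tempting to say that the look falls inside the first transmission season. The dates do not support this. Follow-up starts in July or August 2023 and the peak runs May to October, so 4 to 6 months later is November to February. It does fall before the second peak.

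Nor does the text show that the calendar governs: it sets the event count as the rule and gives Year 1 only as an estimate. The power analysis is left to the statistical analysis plan, which is not shown, but the trigger, label, date and boundaries are all stated in the protocol and conflict there.

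**Conclusion.** The point holds and should be fixed, though it does not threaten the validity of the test. The stated rate, trigger and date cannot all be true: event 658 is expected at about 6 months on the inputs that reproduce 1315. This does not depend on how much of k remains. It assumes constant hazards and loss applied as a 20% reduction; late or no loss makes it 4 to 5 months.

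The 50% label is wrong for a first-event analysis with any residual clustering: about 0.88 at k = 0.40 and 0.58 to 0.82 for k of 0.1 to 0.3. If all episodes are analysed it is about 0.80 or lower. The crossing chances of 47% and 2%, against 23% and 9% at a true half-information look, rest on k = 0.40 and PE 35%. The practical consequence is an efficacy claim that could rest on about 6 months of data, with futility crossed far less often under the design effect than a half-information look implies.

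**What to change.** Reconcile the event count, event type, calendar estimate and information label, before the look is taken.

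- Choose one trigger and state it as the rule: for example calendar month 12, if the end of Year 1 is what is wanted, or a stated level of model-estimated information.
- State whether first or all episodes count, for both 1315 and the interim, in line with the primary model.
- Define information as 1/s² from the fitted random-effects model.
- Recompute the efficacy, futility and final values from the spending function at that information.
- Restate the early-stopping probabilities.

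A month-12 look would carry about 0.89 to 0.97 of the information for residual k of 0.2 to 0.4. It gives longer follow-up before the look but does not restore a half-information look. Spending at calendar fraction 0.5 gives an efficacy value of 2.963, and at k = 0.40 and PE 35% the chance of crossing it is still about 46%.

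The cost is recalculation and wording, with no added children or visits. With a month-12 trigger, the look is later than the event count would give.
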